**Fig. 1 Fig1:**
[figure not shown]
Schedule of enrolment, interventions, and assessments. Information about the diagnostic measures can be found in themanuscript text. Time points: -t1 = First contact and enrolment to the study; t0 = Baseline assessment; tx = Appassessments; t1 = After 16 weeks, Assessment at the end of intervention treatment group/begin treatment waiting group; t2= After 32 weeks, Follow-up I for treatment group/end of intervention waiting group; t3 = After 48 weeks, Follow-up IItreatment group/follow-up waiting group; t4 = After 48 weeks, Follow-up II waiting group. X means assessment in thetreatment and waiting group unless it is indicated that the assessment is only carried out in one specific group. TG=treatment group; WG = waiting group. p=assessed in parents, c = assessed in children, t =assessed in therapist. * only TG,** only WG

Adherence will be supervised by questionnaires before and after each session, by discussions with the therapist and by continuous supervision of homework. Participants get written instructions for all technological procedures. Any missing data, homework, and other problems concerning the intervention are discussed within the study group and patients are then approached by strategies to increase compliance.

Participant retention is ensured by a good contact between all team members and the participants. If participants do not complete follow-up assessments, they are reminded by the study team or their therapist several times. Participants are also encouraged to follow the planned interventions; however, if other interventions might be more appropriate, they will be transferred to other treatment options. The patients agree to participate in the study and the associated follow-up interviews by means of the consent forms. Intrinsic motivation is triggered by the timely participation in the therapy by experts within the framework of the study and the reduction of the obsessive-compulsive symptoms through the treatment in the study, and extrinsic motivation is the encouragement by the diagnostician to carry out the follow-up interviews. There is no financial compensation for the patients.

The documentation of the follow-ups including questionnaires will be recorded manually in the respective patient folders and kept locked in the cabinets in the clinic. If participants do not at all adhere to the protocol, are not motivated, or want to quit the study, they will drop out of the study; however, this will be the last option and motivational work will be done in advance. All planned outcomes will, nevertheless, be assessed for dropouts. A digital list of dropouts is kept within the study team and we note the reason for their dropout. Information about non-compliance, problems, or harms are continuously documented during the trial after every treatment session.

Data collection is monitored by our study team who meets every week. If problems with data collection become obvious, the team decides together about required next steps to ensure data quality, e.g., telephone call with the participants to encourage data completion. There is no external supervision of the data. As we use a low-risk intervention, there will be no trial auditing. As mentioned, the project team meets every week to discuss trial conduct.

There are no planned interim analyses that might lead to trial finalization. Trial would be stopped only if the team observes severe clinical reasons to stop the trail. These are, however, not expected because of our preliminary study and the fact that treatment is based on state-of-the art therapy methods. Data are in part only evaluated when needed, for example to show first preliminary results in presentations on conventions. If there are any changes to the protocol, these are discussed within the study team and the sponsor and changes are documented. If the protocol must be changed, the trials registry ClinicalTrials.gov will be updated. Only the study team has access to the final dataset.

Results will be disseminated in scientific papers, presentations in conventions, or within the university hospital or public media. Additionally, the funder will be informed about the results.

### Questionnaires and interviews

Figure 1 depicts the time points of measurement and source of all dependent variables.

#### Primary outcome

The Children’s Yale-Brown Obsessive Compulsive Scale (CY-BOCS) [40] will be used for the assessment of OCD symptoms and treatment response. The CY-BOCS is a clinician-administered instrument that evaluates obsessions and compulsions. The primary assessment endpoint is the comparison between the treatment and waiting group at t1.

#### Secondary outcomes

The Child Obsessive-Compulsive Impact Scale (COIS-RC) is a 33-item self-report questionnaire to the impact of OCD symptoms on the psychosocial functioning of the children [41]. With a *sociodemographic questionnaire*, we will assess basic variables such as age, sex, course of the disorder, family situation, and school. The Schedule for Affective Disorders and Schizophrenia for School-Age Children Present and Lifetime Version (K-SADS-PL) [42] as a semi-structured clinical interview will be used for diagnostic assessments of a wide variety of psychiatric disorders. Clinical Global Impressions-Severity (CGI-S, SCI-I) is a clinical 7-point rating scale of symptom severity [43]. *The Youth Self Report (YSR/11-18R)* is a 112-item 3-point scale completed by the children themselves and addresses a variety of behavioral and emotional problems [44]*. Child Behavior Checklist* (CBCL/6-18R), the CBCL, is a 113-item 3-point questionnaire for parents that assesses a wide range of child behavioral and emotional problems [45]. Screen for Child Anxiety Related Emotional Disorders (SCARED): The SCARED assesses DSM-IV anxiety symptoms [46]. Questionnaire for Measuring Health-Related Quality of Life in Children and Adolescents (KINDL/Kiddo KINDL) is a 24-item 5-point scale self-report questionnaire for children and parents to quality of life [47]. With the *Lebensqualitäts-Inventar für Eltern chronisch kranker Kinder* (ULQIE), we will assess life quality of parents related to the impairment through the illness of the child [48]. Culture-free test (CFT-20-R) to assess cognitive functioning is used as a test for intelligence [49]. The *Depressionsinventar für Kinder und Jugendliche* (DIKJ) will measure depressive symptoms in the children. It has 26 items and a 4-point scale [50]. We assess emotional, cognitive, and behavioral e*ngagement at school* with 5 items each filled out by the children and adolescents [51].

#### Other outcomes

The Junior Temperament and Charakter Inventar (JTCI/12-18R/JTCI/7-11R) assesses temperament characteristics with 103/86 items and a 5-point scale [52]. To assess the core personality traits of children until 12 years, the parents will fill out the HEXACO- Elementary School Inventory (HEXACO-ESI). Adolescents (12 years and older) complete according items from a middle school inventory themselves (HEXACO-JU) based on the HEXACO model of personality factors [53]. For another study, we will also assess trauma questionnaires to answer trauma-related questions: The *Childhood Trauma Questionnaire* (CTQ) as a 5-point scale and 28 items measures trauma experience such as sexual abuse or emotional neglect [54]. Furthermore, we will assess the *Essener Trauma Inventar für Kinder und Jugendliche* (ETI-KJ) for posttraumatic symptoms [55] as well as the *Trauma History Questionnaire* (THQ) as a 24-item measure of traumatic events [56].

#### Session questionnaires

After each session, we will obtain information about the following: (a) impairment through specific OCD symptoms, (b) questions about satisfaction with the session and (c) the patient-therapist relationship, (d) questions about homework compliance and technical problems, (e) information about missed sessions, (f) deviations from the manual, and (g) session length. With a post-experimental questionnaire, we will ask for satisfaction about different elements of the therapeutic intervention, such as (a) manual, (b) technique, (c) patient-therapist relationship, (d) improvement, (e) problems, (f) preference over traditional therapy approaches, and (g) decisions about useful therapy elements. These questions were also partially derived from questionnaires about treatment fidelity, acceptability, integrity, and engagement such as Session Integrity Checklist (SIC) used by Kazdin and colleagues [57], the Manual Rating Form (MRF developed by Kendall and colleagues [58], a Therapist Feedback Form (STFF), barriers to treatment scale (BTPS [59]), a consumer satisfaction questionnaire (TAI, [60]), and the Client Satisfaction Questionnaire-8 (CSQ-8 [61]). We will also collect information to premature dropouts and ask participants whether they agree to fill out our post-experimental questionnaires. The therapist will also provide data in post-experimental questionnaires.

### Apps

We will use two apps for the project. The first app is an app with specific questions about the severity of children’s OCD and evaluations of the day or week. We will assess children and their parents with questions to the children’s OCD symptoms and impairment, avoiding behavior, mood, quality of the day, and daily hassles every day (in the evening). Furthermore, once a week, we will obtain in children’s and parents’ information about symptom development. Finally, the app prepares and evaluates exposures as well as levels of distress before, during, and after the exposures as well as avoiding behavior. Data of this app will be used for the therapy sessions and is discussed with the families. The second app will be a physiology app that connects the smartphone with a physiology wristband (BEURER AS 97). This app sends markers (e.g., beginning and end of exposures, beginning and end of bed time) and transfers the physiological data to save local storages at the university hospital. Data quality and entrance of the data into the hospital’s safe databases is continuously supervised and patients are reminded to complete the questions if they forgot it.

### Psychophysiology

To ensure objectivity of data while using a BEURER AS 97 wristband, we will assess heart rate and activity (body movements) to indicate distress levels in the children during one afternoon until the morning for 1 day during the week and 1 day during the weekend [62]. Additionally, we will assess baseline physiology before each therapy session to register distress levels. Activity levels during sleep will estimate sleep quality.

### Manual/therapy sessions

The psychotherapy sessions will be conducted by experienced psychological psychotherapists and they resemble classical in-office psychotherapy with the exception of the usage of teleconferences with the software Vidyo and the additional availability of data for the therapeutic procedure assessed by the app. For the teleconferences, patients will use a tablet and home WIFI and for the app a Samsung Galaxy A5/A50 smartphone with mobile internet provided by the study team. In addition, children will wear a Beurer active AS 97 wristband to measure physiological data. The therapy consists of 14 weekly sessions which each last around 90 min, completed within 16 weeks. The procedure and content of the therapy including material are based on the behavioral therapeutic manual of Wewetzer and Wewetzer [63]. Work sheets will be provided through the cloud BW sync&share; however, this service will soon end for our department. Therefore, a cloud system from our clinic will also be provided whereby each patient and family have their own folder, where they can upload completed material. The treatment will start with psychoeducation, followed up by cognitive interventions and exposure therapy starting in session 4 in combination with response prevention and cognitive therapy. At the end of treatment, there will be two sessions with additional elements for relapse prevention. Each session starts with questions to homework and technical problems. Before each session, the therapist will evaluate the app data from during the week and discuss relevant points with the children and later also the parents. During the session with the child, patient and therapist will work on exposures and cognitive elements. The session will include elements where the children are alone and where the parents are alone and all together depending on children’s age. At the end, there is also some contact with the parents. After every session, patients, parents, and therapists will answer the questionnaires of the session online. More information about the manual can be obtained from the authors. If there are any events that lead to the conclusion that our patients should need another form of treatment, we will lead them to a more suitable treatment option. Any adverse events, protocol injuries, or unexpected events will be noted, followed up by an internal consultation and decision about the subsequent procedure with all members of our team.

### Technical equipment

We will use the home WiFi access for the teleconferences which are provided via the software Vidyo on tablet, display 10.1 inch 1920 × 1200 IPS, CPU: Qualcomm Snapdragon 625, Memory 4 GB, Storage 64 GB, OS: Android 7.1.1 offered and configured by our department. Therapists will use computers with webcam in their offices at the department. Children and parents will also receive configured smartphones with the questionnaires and the physiology app and mobile internet data packages. Therapy materials are provided via the cloud bwSync&share/Clinic cloud. Physiological data is assessed with Beurer AS97 wristbands.

### Data security concept

We will conduct the study in collaboration with the IT department and data security specialists of our university. The data security concept is available from the authors upon request. The smartphones and tablets are secured with passwords and a software to block undesired internet platforms. The password is only exchanged with the families when required because of technical problems. Families have to sign that they ensure that they use the hardware safely only for study purposes and taking care to protect their data. Data of the app will be safely transferred to intermediate servers and from there to servers in the hospital, all encrypted and secured with firewalls. There is no long-term storage of data on the smartphone. After study leave, all devices will be newly configured. An overview over the used Integrated Mobile Health Research Platform (IMeRa) can be found on the following website: http://www.medizin.uni-tuebingen.de/nfmi/imera/imera_start.html. Worksheets and other therapy material will be exchanged between the therapist and the families via the safe clouds bwSync&Share/clinic cloud. Individuals get password-protected folders. All data will be stored using pseudonyms. Apps and cloud folders will be protected from people who are not part of the study team accessing the data. Regular data entry into the databases are continuously checked by our team members. Both apps were developed by the IT department. The reasons for this were data protection and the avoidance of unwanted data manipulation (e.g., extrapolation or smoothing of measured values).

### Statistical analysis

We will use SPSS for data analysis. For all diagnostic parameters, we will assess treatment efficiency with ANOVAs with group as the between-subject factor (treatment group (experimental group), waiting group (control group)) and time (t0 = diagnostic assessment, t1 = end of treatment treatment group/end of waiting period, t2 follow-up I treatment group/ end of treatment waiting group, t3 follow-up II treatment group/follow-up I waiting group, t4 follow-up II waiting group) as the within-subject factors. The most important outcome analysis will be the comparison in CY-Bocs score between the treatment and waiting group at t1. A comparable repeated measures ANOVA will be conducted for the time between t0 and t1 concerning weekly app questions/aggregated physiological data over the week but the time factor is week 1 to week 14. This is to indicate weekly symptom course and differences to the data assessed during waiting in the waiting group. Deeper analyses will concentrate on symptom course and intra-individual variability for daily app questions. Answers of child, parents, and therapist are correlated to investigate their agreement. Additionally, we will evaluate if avoidance behavior during exposures is related to treatment success within exposures with correlations of severity of avoidance behavior and anxiety decrease during exposures. We will also evaluate the influence of avoidance behavior during exposures and during the day on symptom decrease over the treatment assessed via CYBOCs with correlations. Descriptively, we evaluate the answers of our post-experimental questionnaire to treatment compliance, feasibility, and satisfaction as well as the within session questions. We will also compare the number of dropouts between the experimental group and the waiting group with *t*-tests. Integrity is descriptively evaluated with the session questionnaires provided by the therapist. Data will be analyzed to see if missing values are correlated with any basic effects. Little’s Missing Completely at Random Test (MCAR) will be used to check whether they are randomly distributed. The recommendations of the National Research Council will be followed. If there are missing data, we will report analyses with all data available. There will be enough data for the comparison between t0 and t1. A second set of analyses will also include the follow-up assessments where some missing data might appear. We might additionally report analyses with imputations. Significance will be followed up with Bonferroni-corrected paired contrasts. Alpha level is 5% and all tests will be conducted two-tailed.

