The participants will be assigned to the treatment or waiting group by block randomization according to the order of incoming calls. The randomization list is computer-generated and randomized to assign subjects to both groups in equal proportions. The randomization list was developed by our Institute for Clinical Epidemiology and Applied Biometry (IKEaB) with 8 blocks of 6 participants, consisting of *n* = 3 participants as waiting group and *n* = 3 participants starting treatment directly. The diagnostic expert will be blinded to the group condition. The assignment of the subjects will be pseudonymized by the randomization list, so that the diagnostician does not know which child is assigned to which group. The randomization list will be stored in a sealed envelope in the cabinet. After the patients are assigned to either the waiting or treatment group by block randomization according to the sequence of calls and inclusion in the study, they receive feedback on the allocation from a therapist from our study team. For this purpose, the therapist looks into the sealed envelope containing the order of the randomization list. This feedback is given either by telephone call or in person during the meeting on site at the clinic.

In the treatment condition, there are 14 weekly teleconference psychotherapy sessions lasting approximately 90 min each. Post-assessment will take place face-to-face. A total of 16 weeks after the treatment, there will be a first follow-up with clinical questionnaires that are sent to the families and a teleconference-based diagnostic session. A second follow-up will take place after another 16 weeks to further evaluate the effects and to enable comparing of the progress between treatment and waiting list group.

For the treatment group, outcomes will be evaluated before randomization (baseline, t0), after 16 weeks (end of treatment, t1), 32 weeks after randomization (follow-up I, t2), and 48 weeks after randomization (follow-up 2, t3). For the waiting list group, outcomes will also be measured before the first randomization (baseline, t0), at 16 weeks (waiting list period, t1), at 32 weeks (end of treatment, t2), at 48 weeks after the first randomization (follow-up I, t3) (compare Fig. 1), and at 64 weeks after the first randomization (follow-up II, t4).

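### The group-by-time ANOVA over t0–t4 cannot be estimated because the treatment group has no t4, and its t2–t3 levels compare immediate with delayed treatment

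*Protocol article*

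**What the plan says.** All references are to the protocol article.

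- **Model.** The Statistical analysis section states: "For all diagnostic parameters, we will assess treatment efficiency with ANOVAs with group as the between-subject factor". The within-subject factor is time with five named levels, t0 to t4, the last two being "t3 follow-up II treatment group/follow-up I waiting group, t4 follow-up II waiting group) as the within-subject factors".
- **Schedule.** In Study procedure and design, the treatment group's visits after t1 are at "32 weeks after randomization (follow-up I, t2), and 48 weeks after randomization (follow-up 2, t3". Only the waiting group has a further visit, "and at 64 weeks after the first randomization (follow-up II, t4". The Methods part of the abstract gives the same schedule.
- **Primary contrast.** The Subjects, Primary outcome and Statistical analysis sections all name the between-group CY-BOCS comparison at t1 as primary or most important.
- **Follow-up visits.** After a remark that data will suffice for t0 versus t1, the text adds: "A second set of analyses will also include the follow-up assessments where some missing data might appear". It gives no separate model for this second set.
- **Testing.** "Significance will be followed up with Bonferroni-corrected paired contrasts", with a two-tailed 5% level. The software is SPSS.
- **Figure.** The Fig. 1 legend reads "t4 = After 48 weeks, Follow-up II waiting group", against week 64 elsewhere.

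**The concern.** The one group-comparison model given for the diagnostic parameters includes a time level that one group never reaches. Whoever runs the analysis must depart from the text: drop t4, drop t2–t4, realign visits by treatment phase, or change the type of model. These choices answer different questions. The protocol does not say which applies, and it allows preliminary results to be shown at conventions, so an unwritten choice could be made with some results already known.

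Once t4 is removed, the remaining visits still mix two comparisons. The groups differ in whether they have been treated only at t1. From t2 onwards they differ in when they were treated. A group effect or omnibus interaction over t0–t3 therefore cannot be read as the effect of treatment against waiting, although the section presents the ANOVA as its assessment of efficacy.

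**Working it through.** **1. What each visit compares** (Study procedure and design)

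| Visit | Week | Treatment group | Waiting group |
|---|---|---|---|
| t0 | baseline | untreated | untreated |
| t1 | 16 | end of treatment | end of waiting, untreated |
| t2 | 32 | follow-up I | end of treatment |
| t3 | 48 | follow-up II | follow-up I |
| t4 | 64 | no visit | follow-up II |

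**2. Estimability.** Two groups by five visits need 2 × 5 = 10 cell parameters. Nine cells can be observed, and the design matrix has rank 9. The full interaction and the group effect averaged over five visits are not estimable. Under complete-case repeated-measures ANOVA, patients with all of t0–t4 number 0 in the treatment group and at most 20 in the waiting group (20 per group is the planned analysed number), so the group factor disappears. Available-data analysis can still estimate contrasts at t0–t3, but it cannot fill an unscheduled cell. Imputing the treatment group's t4 would create a visit that was never planned.

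**3. Terms over t0–t3.** The protocol states no power, so there is no figure to reproduce. Inputs from the Subjects section: 20 per group and d = 1.001, the effect cited from an adult waiting-list study. Assumptions that are not in the documents: both groups reach the same level once treated, unit variance, and equal correlation r between visits of 0.3 to 0.7.

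- Direct t1 comparison: noncentrality 1.001 / √(2/20) = 3.17; power 0.870 at two-sided 5% (38 df).
- Group main effect: average difference (0 + 1.001 + 0 + 0)/4 = 0.25. The variance of a patient's four-visit mean is (1 + 3r)/4. At r = 0.5 the noncentrality is 0.25 / √(0.1 × 0.625) = 1.00.
- Simulated power (3,000 runs per row):

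| r | Group main effect | Group × time, 3 df | t1 t-test |
|---|---|---|---|
| 0.3 | 0.208 | 0.766 | 0.864 |
| 0.5 | 0.174 | 0.909 | 0.865 |
| 0.7 | 0.149 | 0.992 | 0.869 |

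The main effect is diluted to a quarter of the t1 effect. The interaction keeps its power but is not specific: it responds to any difference in course, including one at t2 or t3 that arises only from the timing of treatment.

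**4. Status of the t1 test.** The section names the t1 comparison but attaches no test to it, and the stated route from a significant ANOVA is Bonferroni-corrected contrasts. If t1 were one of four such contrasts (the factor of four is an assumption), the level would be 0.05/4 = 0.0125 and power 0.704 instead of 0.870.

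**The case against.** The strongest reply is that the primary analysis is untouched. The t1 CY-BOCS comparison is named in three sections. The Statistical analysis section sets t0–t1 apart from a second set of analyses that adds the follow-ups, and its plural ANOVAs can be read as covering both sets. This stands: the primary contrast is identifiable and can be run. It does not rescue the model as written, because no different model is given for either set and the five-level factor is stated for all diagnostic parameters.

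Some stronger readings are tempting and are not supported:

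- **That efficacy power collapses to 15–21%.** That figure belongs to the group main effect, which the protocol never names as its test. The interaction, the usual term in such a design, keeps 77–99% under the same assumptions.
- **That Bonferroni lowers the primary test's power to 70%.** The text gives neither an omnibus gate for t1 nor a factor of four. It is ambiguous, not contradictory; paired contrasts may even mean visit pairs within patients.
- **That t1 is the only randomised contrast.** Groups at t2 and t3 are still as randomised. What is lost is treated versus untreated. Study procedure and design says the second follow-up is meant to allow progress to be compared between groups, so a between-group follow-up analysis is legitimate if labelled correctly.
- **That the authors regard the absent t4 as ordinary missing data.** The remark on missing data concerns follow-ups in general, and the same section assigns t4 to the waiting group.

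**Conclusion.** The concern holds for the ANOVA as specified and should be fixed. The empty t4 cell follows from the protocol's own schedule and needs no assumption: rank 9 for 10 parameters, and no complete cases in the treatment group. That t2 and t3 compare immediate with delayed treatment also follows from the schedule. The power figures illustrate dilution and non-specificity. They rest on the assumed catch-up pattern, the assumed correlations and the cited d = 1.001.

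A reader should not infer that the trial's primary result is at risk. For t1 the defect is limited to unclear wording on whether the test is direct at 5% or a corrected contrast. The Fig. 1 week for t4 is a labelling slip without analytic consequence, since the legend still gives t4 to the waiting group only.

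**What to change.** 1. Limit the efficacy model for CY-BOCS and the other diagnostic parameters to t0 and t1.
2. State that the between-group CY-BOCS comparison at t1 is tested directly at two-sided 5%, with no preceding omnibus test and no Bonferroni factor, and say which contrasts the correction does cover.
3. Report t2 and t3 separately, labelled as immediate versus delayed treatment, or aligned by treatment phase (pre, post, follow-up I, follow-up II) in a mixed model, or both. Do not present them as treatment-versus-waiting efficacy. If aligned by phase, state which visit is the waiting group's pre-treatment score.
4. Use t4 only within the waiting group or in the phase-aligned model.
5. Reconcile the Fig. 1 legend with the 64 weeks in the abstract and in Study procedure and design.

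The cost is analysis wording and one figure label. No further data are needed, and mixed models are available in SPSS, the software already planned. The change should be recorded before the group comparisons are run.

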## Methods/design

### Subjects

The study has a parallel group design with an experimental group receiving treatment after baseline assessment and a waiting group receiving treatment after a waiting period of 16 weeks, comparably to the length of treatment. The planned allocation ratio is one expecting superiority in symptom reduction in the experimental group. Patients are recruited by licensed child and adolescent psychotherapists who work at the university hospital of Tübingen. A Google AdWords advertising and recruitment campaign is carried out in cooperation with the Department of Communication at the University Hospital Tübingen.

To deal with probable dropouts, we planned to enroll 30 children with OCD in the experimental group and 30 children with OCD in the waiting group with the aim to finally analyze 20 patients in each group. Including clinical considerations, this was a realistic sample size, we were able to achieve in a 3-year period. Sample size was planned according to the following considerations. As primary outcome, we considered the CY-Bocs score. Our primary assessment endpoint was the comparison at t1 post-treatment between the treatment and the waiting group. In the pilot study of our treatment protocol using a pre/post-assessment with *N* = 9 children with OCD [38], effect size was *d* = 2.02. Therefore, we knew, that our treatment protocol most likely will lead to symptom reduction. Effect size of another study comparing webcam-delivered CBT in 16 children with OCD with a waiting group of 15 children with an ANCOVA on post-treatment CY-Bocs scores, covarying baseline CY-BOCS scores, showed a significant effect of treatment with *η*^2^ = 0.36 [37]. A further study in adults with OCD [39], comparing face-to face exposure treatment (*n* = 20) with a waiting group (*n* = 16), revealed an effect size of *d* = 1.001 for the CY-Bocs comparison at post-treatment. Therefore, we estimated that the effect in our study as a comparison of CY-Bocs scores of an effective treatment in comparison to the waiting group at t1 will be high. We expected that there will be a significant difference comparing 20 patients with treatment with 20 patients in the waiting group at t1.

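### The primary CY-BOCS comparison at t1 does not use baseline CY-BOCS as a covariate; the test is valid, but ANCOVA would gain precision at almost no cost

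*Protocol article*

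**What the plan says.** Under Primary outcome, the article sets the endpoint: "The primary assessment endpoint is the comparison between the treatment and waiting group at t1". Under Statistical analysis, it gives one method for all diagnostic measures: "we will assess treatment efficiency with ANOVAs with group as the between-subject factor", with time (t0 to t4) as the within-subject factor. It then singles out the key test: "The most important outcome analysis will be the comparison in CY-Bocs score between the treatment and waiting group at t1". No covariate is named for it.

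Under Study procedure and design, the t0 assessment precedes allocation in both arms; for the treatment arm the text reads "For the treatment group, outcomes will be evaluated before randomization (baseline, t0". A CY-BOCS score above 16 is also an entry criterion, so a baseline value exists for every randomised child.

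The sample-size paragraph under Subjects cites three effects:
- the investigators' pilot, N = 9, a pre/post d of 2.02 ("In the pilot study of our treatment protocol using a pre/post-assessment with");
- a webcam-CBT trial in 16 versus 15 children, "with an ANCOVA on post-treatment CY-Bocs scores, covarying baseline CY-BOCS scores, showed a significant effect of treatment with" an eta-squared of 0.36;
- an adult face-to-face study, 20 versus 16, with d = "1.001 for the CY-Bocs comparison at post-treatment".

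It concludes that the effect will be large and that 20 analysed per group should suffice. No target power is stated.

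**The concern.** In a group-by-time ANOVA, the baseline score is an outcome level. The group contrast at t1 in such a model takes no account of where each group started. The interaction restricted to t0 and t1 is a change-score test, which subtracts the whole baseline difference whatever the correlation. ANCOVA estimates how much of the baseline difference to remove.

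With about 20 children per group, two things are at stake. One is precision, because variation in t1 scores that baseline could explain stays in the error term. The other is protection against chance baseline imbalance, which the blocked randomisation, described without stratification by severity, does not control. Recruitment is closed (Trial status), so any further precision has to come from the analysis.

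**Working it through.** **Inputs.** From the article: 20 analysed per group, 1:1 allocation, two-sided alpha 5%, d = 1.001 (the post-treatment comparison) and eta-squared = 0.36 (the ANCOVA). Assumed, because the article gives none: within-group correlation r between t0 and t1 CY-BOCS of 0.3, 0.5 and 0.7, with equal variances at t0 and t1.

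**1. The plan's own figure.** No target power or single design effect is stated, so 20 per group cannot be reproduced as a derivation. At d = 1.001 the noncentrality is 1.001 / √(2/20) = 3.17. With 38 degrees of freedom, power is 87.0%.

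**2. Does the ANCOVA planning effect leave the unadjusted test short?** f = √(0.36/0.64) = 0.75, so d = 2f = 1.50 on the baseline-adjusted scale. On the unadjusted scale this is 1.50 × √(1 − r²) = 1.43 / 1.30 / 1.07. Power of the unadjusted t1 test is then 99.3 / 97.9 / 91.0%. There is no shortfall.

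**3. Three candidate tests at d = 1.001.** The variance factors relative to t1-only are 1 for t1-only, 2(1 − r) for the change score and 1 − r² for ANCOVA. The standardised effects are:
- t1-only: 1.001 throughout
- change score, 1.001/√(2(1 − r)): 0.846 / 1.001 / 1.292
- ANCOVA, 1.001/√(1 − r²): 1.049 / 1.156 / 1.402

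The factor 1 − r² ignores the cost of estimating the slope from 40 children. On average that cost multiplies the variance by 37/36, and one degree of freedom is lost (critical t 2.026 instead of 2.024). The interval-width ratio of ANCOVA to t1-only is therefore √((1 − r²) × 37/36) × 2.026/2.024. Simulation of the three tests agreed with these ratios and gave the ANCOVA power below.

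| r | Power, t1-only | Power, change score | Power, ANCOVA | ANCOVA interval vs t1-only |
|---|---|---|---|---|
| 0.2 | 87% | 68% | 87% | under 1% narrower |
| 0.3 | 87% | 74% | 89% | 3% narrower |
| 0.5 | 87% | 87% | 94% | 12% narrower |
| 0.7 | 87% | 98% | 99% | 28% narrower |

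At r = 0.1 or 0 the ANCOVA interval is about 1% wider. At r = 0.5, 20 per group with ANCOVA is worth 20/(0.75 × 37/36), or about 26 per group unadjusted.

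**4. Chance imbalance.** The standard error of the baseline difference is √(2/20) = 0.316 SD. A difference above 0.3 SD has probability about 34%, and above 0.5 SD about 11%. Given a 0.5 SD imbalance, the t1-only difference shifts by r × 0.5 = 0.15 / 0.25 / 0.35 SD. The change score over-corrects by (1 − r) × 0.5 = 0.35 / 0.25 / 0.15 SD.

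**The case against.** The case against giving this much weight is strong in several respects.

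A reader might infer that the sample size rests on an ANCOVA effect that the planned analysis cannot reproduce. The article does not support that. Only one of its three effects is covariate-adjusted. The smallest, d = 1.001, is described as a post-treatment comparison with no adjustment mentioned, which matches the planned t1 test. Step 2 shows that even the ANCOVA effect leaves the unadjusted test with at least 91% power for r up to 0.7.

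A reader might also infer that the unadjusted test is biased or invalid. It is neither: randomisation makes it unbiased on average, and its standard error already allows for chance imbalance.

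The gain depends on an unknown correlation, and the entry threshold of CY-BOCS above 16 restricts the baseline range and may keep that correlation low. At 0.2 or below there is practically nothing to gain over t1-only. Baseline is also not ignored altogether, since t0 is a level of the ANOVA.

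Finally, this is a condensed article, and a separate analysis plan may name covariates. That weakens the point without removing it, because the article does state its method, and the method is ANOVA. All of these qualifications stand. None gives a reason to prefer the stated test over ANCOVA at correlations above about 0.2.

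**Conclusion.** The point holds as an efficiency improvement that is nearly free, not as an error in the design or the sample size. The stated primary test is valid and has about 87% power at d = 1.001 with 20 per group. ANCOVA raises this to about 89 / 94 / 99% at r = 0.3 / 0.5 / 0.7. It is at least as precise as either the t1 contrast or the t0-to-t1 interaction once r reaches about 0.2. The advantage over t1-only grows with r, while the advantage over the change score is largest when r is low. The size rests on the assumed correlations, equal variances and 20 analysed children per group; the direction does not depend on the value of d.

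**What to change.** Define the primary analysis as ANCOVA: t1 CY-BOCS on group with t0 CY-BOCS as covariate, reporting the adjusted mean difference with its 95% CI. Use the same form for the continuous secondary scales that have a t0 value, each with its own baseline. It does not suit items listed there such as the sociodemographic questionnaire, the diagnostic interview, the intelligence test or an improvement rating. The group-by-time ANOVA can remain for describing the course over follow-up.

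Inclusion has ended, and the article allows data to be looked at early for presentations. The change should therefore be a dated, documented amendment with a registry update, made before the group comparison is run, and it should say whether any comparative t1 data have already been seen. It needs no new data. The statistical cost is one degree of freedom, plus a slight loss of precision if the correlation proves to be near zero.
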